#### Group B streptococcus

We are not aware of any studies of a probiotic treatment effect on GBS carriage on which to base power calculations but the New Zealand prevalence was reported to be 22 % in 1998-9 [46]. With a sample size of 200 in each group and a 2.5 % drop-out rate, the study will have 84 % power to detect a reduction to 11 % at a 5 % level of significance.

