##### BV and GBS

All swabs and blood samples are processed using standard laboratory practices by accredited medical laboratories in the study centres. Vaginal swabs for BV and vagino-rectal swabs for GBS are self-collected by woman at enrolment (baseline) and 35–37 weeks gestation (outcome) following standardised written instructions and using Copan Transystem Amies (Ref 108CF.FR) swabs. Additional file 1: Figure S1 shows the swab collection instructions in more detail. After collection, swabs are transported at ambient temperature to laboratories as soon as is possible but within a maximum of 24 h. BV swabs are gram stained, and reported according to the three bands of Nugent’s scale, (0–3 being normal, 4–6 intermediate, and 7 or more indicating BV) [70]. GBS swabs are reported according to the presence or absence of GBS. As GBS is not treated in early pregnancy and BV is only treated if symptomatic, the results of baseline swabs remain confidential to the study. This is to ensure study swabs do not unintentionally result in unrequired antibiotic treatment being prescribed by reporting positive swabs which may not be from symptomatic disease. Only the results of the outcome 35–37 week GBS swabs are shared with the woman’s lead maternity carer (LMC)^1^ as these swabs inform the woman’s clinical care.

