### Data analysis

An intention-to-treat analysis will be used to assess the effect of HN001 on the 12 month cumulative prevalence of eczema and SCORAD ≥10 using hazard ratios from a Cox’s proportional hazards model, and the point prevalence of atopy at age 12 months using relative rates and a chi-squared test. Chi-square test will also be used to compare the proportion in each study group with detectable levels of immunological markers in breast milk and for those with detectable levels, t-tests will be used to compare the groups if the data is log-normally distributed. If the data is not log-normally distributed a Wilcoxon Rank-Sum test will be used. Where there are important differences between groups, these variables will be added to the models to assess whether these variables mediate any effect of HN001 on eczema and/or atopic sensitisation (using a generalised linear model with a log link and binomial distribution). The association of HN001 with the presence of GDM, BV and GBS will be assessed using relative rates and chi-squared tests. EPDS and State Anxiety Inventory will be compared with a Wilcoxon Rank-Sum test. The effect of weight gain will be investigated as an intermediate variable by adding it to the model (a generalised linear model with a log link and binomial distribution) in the GDM analysis. Any baseline differences that occur will be adjusted for. If commercially available non-study probiotics have been used, a sub-group analysis will be performed after excluding this group, which we do not expect to be large. Reasons for withdrawal from the study will be recorded and examined for differences between study groups. Adjustment will be made for differences in antibiotic use between study groups. SAS version 9.4 will be used.

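### BV and GBS are swabbed at enrolment, but the 35–37 week comparison is a plain chi-squared test and the baseline result enters only if a group difference happens to be seen

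*Protocol article*

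**What the plan says.** The BV and GBS section of the protocol article states that the vaginal and vagino-rectal swabs "are self-collected by woman at enrolment (baseline) and 35–37 weeks gestation (outcome"). Table 2 shows the same two time points. Enrolment is the visit at which the capsules start.

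For the analysis, the Data analysis section states: "The association of HN001 with the presence of GDM, BV and GBS will be assessed using relative rates and chi-squared tests". It names no covariate or stratum for these comparisons. Two general sentences later in that section could bring in other variables: "Any baseline differences that occur will be adjusted for" and "Adjustment will be made for differences in antibiotic use between study groups". A log-link binomial model is named there, but only for mediation of the eczema and sensitisation effects and for weight gain in the GDM analysis.

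For GBS, the sample size section notes that "the New Zealand prevalence was reported to be 22 % in 1998-9" and concludes that "the study will have 84 % power to detect a reduction to 11 % at a 5 % level of significance", with 200 women per group and 2.5 % drop-out. For BV it assumes 30 % on placebo and 6 % on HN001, with power above 95 %.

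**The concern.** When the same binary state is measured before treatment and again as the outcome, the earlier value is a natural candidate for adjustment. Here the article suggests that existing carriage is largely left alone: the BV and GBS section says that GBS is not treated in early pregnancy, that BV is treated only if symptomatic, and that baseline results stay confidential. Some persistence to 35–37 weeks is therefore plausible, and a planned adjustment would use it.

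The article leaves the choice to the observed data. If the groups look different at baseline, an adjustment of unstated form follows; if they do not, the swab goes unused. Two things are at stake. Precision may be lost for GBS. Which of two analyses is reported for a named secondary outcome is also settled after the baseline data are seen, with no rule for what counts as a difference.

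**Working it through.** **Inputs from the article (sample size section).** GBS: 22 % placebo, 11 % HN001, 200 per group, 2.5 % drop-out, 5 % level (taken as two-sided). BV: 30 % and 6 %, same numbers. Analysed per group: 200 × 0.975 = 195.

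**Step 1. Reproduce the stated GBS power (unadjusted, pooled variance under the null).**
- Mean rate (0.22 + 0.11)/2 = 0.165.
- Null SE = √(2 × 0.165 × 0.835 / 195) = 0.0376.
- Alternative SE = √((0.22 × 0.78 + 0.11 × 0.89)/195) = 0.0372.
- z = (0.11 − 1.96 × 0.0376)/0.0372 ≈ 0.977, so power = 83.6 %.
- The unpooled formula gives 84.1 %. The stated 84 % is therefore the power of the plain two-sample test.

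**Step 2. Assumptions for the stratified test.** The article gives no figure for persistence, so a range is used. Let a be the probability that a baseline-positive placebo woman is positive at 35–37 weeks. Baseline prevalence is set to 22 %, and the placebo outcome rate is held at 22 %. The rate in baseline-negative placebo women is then b = (0.22 − 0.22a)/0.78. The relative rate is 0.5 in both strata.

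**Step 3. Mantel-Haenszel power.** Let m be the expected number per group in a stratum (42.9 baseline-positive, 152.1 baseline-negative), r and r₁ the placebo and HN001 rates, and p their mean. Then
- D = Σ (m/2)(r − r₁)
- V₀ = Σ (m/2) p(1 − p)
- V₁ = Σ (m/4)[r(1 − r) + r₁(1 − r₁)]
- power = Φ((D − 1.96√V₀)/√V₁)

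D is always 97.5 × 0.11 = 10.725. Worked case a = 0.6, so b = 0.113:
- V₀ = 21.45 × 0.45 × 0.55 + 76.05 × 0.0846 × 0.9154 = 5.31 + 5.89 = 11.20
- V₁ = 10.725 × (0.24 + 0.21) + 38.025 × (0.1001 + 0.0532) = 4.83 + 5.83 = 10.66
- z = (10.725 − 1.96 × 3.347)/3.264 = 1.276, power 89.9 %

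| Persistence a (assumed) | b | Stratified power, formula | Stratified power, simulation |
|---|---|---|---|
| 0.22 (no association) | 0.220 | 83.6 % | 83.9 % |
| 0.4 | 0.169 | 85.0 % | 85.5 % |
| 0.5 | 0.141 | 87.0 % | 87.4 % |
| 0.6 | 0.113 | 89.9 % | 90.0 % |
| 0.7 | 0.085 | 93.4 % | 93.1 % |

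Each simulated figure comes from 40,000 trials; the unadjusted test stayed at about 84 % in all of them.

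**Step 4. How often the choice of analysis matters.** In 100,000 simulated trials per scenario at the protocol's GBS effect, the two tests disagreed on significance in about 4 % of trials at a = 0.4, and in 6 % to 11 % at a = 0.5 to 0.7.

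**Step 5. BV.** Mean rate 0.18; null SE = √(2 × 0.18 × 0.82/195) = 0.0389; alternative SE = √((0.30 × 0.70 + 0.06 × 0.94)/195) = 0.0370; z = (0.24 − 1.96 × 0.0389)/0.0370 ≈ 4.43. Power is above 99.9 % without adjustment, and simulation gives the same with it.

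**The case against.** The strongest reply is that nothing here is broken. Under randomisation the chi-squared test is valid whatever the baseline swabs show. The power figures were computed for that test and are correct. Late-pregnancy prevalence is the target set in the study hypothesis. Covariates are often settled in an analysis plan, which is not shown here. All of that stands, except that the article does not simply stay silent: it states a test and an adjustment rule, and that rule is triggered by the data.

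Five stronger readings are tempting and are not supported:
- **That baseline status is ignored.** The general adjustment rule in the same section allows it in when a difference is seen.
- **That chance imbalance biases the result.** The SD of the baseline GBS difference is √(2 × 0.22 × 0.78/195) = 4.2 points. One SD moves the unadjusted difference by 4.2 × (a − b), about 1.5 to 2.6 points at a = 0.5 to 0.7, against a target of 11. The test's error rate already allows for this, and a large imbalance would plausibly trigger the plan's own adjustment.
- **That the swab is the strongest predictor the trial holds.** The article gives no figure on this.
- **That both outcomes lose power.** At the protocol's assumed effect BV does not.
- **That combining persistence with new acquisition is an error.** Prevalence before birth is the stated question; separating the two is a different, exploratory aim.

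**Conclusion.** The point holds as one of precision and prespecification. The named BV and GBS comparison is unadjusted, and the enrolment swab enters only after an undefined difference is observed, through a model that is not named for these outcomes. For GBS, fixing the adjustment in advance would raise power from about 84 % to about 85–93 % if 40–70 % of baseline-positive placebo women remain positive, with baseline prevalence of 22 % and the same relative rate in both strata. The gain is about one point at the low end and nil without association. For BV at 30 % versus 6 % there is no visible power gain, and only the prespecification argument applies. GDM appears in the same sentence of the article but has no corresponding enrolment measurement, so it is outside this point.

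**What to change.** State in advance that the 35–37 week relative rates for BV and for GBS are each estimated with a Mantel-Haenszel analysis stratified by the woman's own enrolment result for that outcome and by study centre (the randomisation stratum), or with a log-link binomial model containing the same terms. Apply this whatever imbalance is seen, and give women without a usable enrolment swab a missing-baseline category. The unadjusted chi-squared result can stay as a supporting analysis. Acquisition among baseline-negative women and persistence among baseline-positive women may be reported as exploratory; the latter would rest on about 0.22 × 195 ≈ 43 women per group at the assumed prevalence.

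The cost is a change of wording. No visit, sample or participant is added, and the stated sample size and power remain correct for the unadjusted test.

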**Methods/design:**

The PiP Study is a two-centre, randomised, double-blind placebo-controlled trial in Wellington and Auckland, New Zealand. Four hundred pregnant women expecting infants at high risk of allergic disease will be enrolled in the study at 14–16 weeks gestation and randomised to receive either *Lactobacillus rhamnosus* HN001 (6 × 10^9^ colony-forming units per day (cfu/day)) or placebo until delivery and then continuing until 6 months post-partum, if breastfeeding.

Primary infant outcomes are the development and severity of eczema and atopic sensitisation in the first year of life. Secondary outcomes are diagnosis of maternal gestational diabetes mellitus, presence of bacterial vaginosis and vaginal carriage of Group B Streptococcus (at 35–37 weeks gestation). Other outcome measures include maternal weight gain, maternal postpartum depression and anxiety, infant birth weight, preterm birth, and rate of caesarean sections. A range of samples including maternal and infant faecal samples, maternal blood samples, cord blood and infant cord tissue samples, breast milk, infant skin swabs and infant buccal swabs will be collected for the investigation of the mechanisms of probiotic action.

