## Methods/design

### Study design and outcomes

The PiP Study is a two-centre randomised double blind placebo controlled trial in Wellington and Auckland, New Zealand designed to test the hypothesis that probiotic supplementation by *Lactobacillus rhamnosus* HN001 (6×10^9^ cfu/day) administered to mothers from 14 to 16 weeks gestation until delivery and continuing until 6 months post-partum, if breastfeeding, will reduce (1) the prevalence of infant eczema and atopic sensitisation by age 12 months and (2) the prevalence of maternal GDM, BV and GBS vaginal colonisation before birth. Table 1 provides an overview of primary, secondary and related outcomes being examined in the study.

**Table 1 Tab1:** Primary, secondary and related outcomes in the PiP Study

Primary outcomes	Related outcomes
1. Infant eczema	Immune and inflammatory markers, epigenetic and metabolomic analyses from cord blood
	Epigenetic analyses on cord tissue
	Genotype and epigenetic analyses on buccal samples
	Immune markers and oligosaccharide profiles from breast milk
	Skin microbiota analysis from neck and axilla skin swabs and gut microbiota analysis from infant faeces
2. Infant eczema severity (SCORAD^a^)	
3. Infant atopic sensitisation	Immune and inflammatory markers, epigenetic and metabolomic analyses from cord blood
	Epigenetic analyses on cord tissue
	Genotype and epigenetic analyses on buccal samples
	Immune markers and oligosaccharide profiles from breast milk
	Skin microbiota analysis from neck and axilla skin swabs and gut microbiota analysis from infant faeces
Secondary Outcomes	Related Outcomes
1. Maternal gestational diabetes mellitus	Maternal:
	Gestation at delivery.
	Maternal anthropometric measures ^b^ at birth, and 6 and 12 months post-partum
	Caesarean section
	Fasting lipids and bile acids from fasting maternal blood taken at time of OGTT
	Gut microbiota and faecal SCFA from maternal faecal samples taken in second trimester
	Infant:
	Anthropometric measures at birth, and 6 and 12 months
	Neonatal intensive care (NICU) admission
2. Maternal BV	Premature rupture of membranes
	Preterm birth (<37 weeks)
3. Maternal vaginal GBS colonisation	Infant GBS
4. Maternal postpartum depression and anxiety	Medication use for emotional/psychological problems
Adverse events and safety	
1. Maternal:	2. Infant:

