#### Gestational diabetes mellitus

Assuming a GDM prevalence rate of 15 %, and based on the study by Luoto [31] which showed a 63 % reduction in prevalence of diabetes mellitus in pregnant women due to a probiotic intervention, with a sample size of 200 in each group and a 2.5 % drop-out rate the study will have 87 % power to detect a difference at the 5 % level of significance.

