### Study assessments

Table 2 provides a summary of the study timeline and investigations. Women enrolled in the study are provided with a study calendar to assist them to prospectively record data relevant to the study questionnaires. Research staff members are trained in standardised administration of all study questionnaires and data collection procedures.

**Table 2 Tab2:** Study timeline and investigations

		14-16 Weeks Gestation	26-28 Weeks Gestation	35-37 Weeks Gestation	Birth	3-7 Days After Birth	Infant Age 3 Months	Infant Age 6 Months	Infant Age 12 Months
	Intervention: new bottle study capsules	✓ Intervention commences	✓			✓	✓	Intervention stops	
	Questionnaire	✓	✓			✓	✓	✓	✓
Objective measures and samples: Maternal									
	Vaginal swab (BV)	✓		✓					
	Vagino-rectal swab (GBS)	✓		✓					
	Anthropometry^a,b,c,d^	✓				✓		✓	✓
	Blood samples (OGTT and serum)		✓^e^						
	Faecal sample		✓						
	3 day food diary		✓						
	Cord blood and tissue				✓				
	Breast milk					✓			
	Skin prick test							✓Completed after birth	
Objective measures and samples: Infant									
	Anthropometry^a,b,c^					✓		✓	✓
	Eczema							✓	✓
	SCORAD							✓	✓
	Faecal sample								✓
	48 hour food diary								✓
	Buccal sample								✓
	Skin swabs								✓
	Skin prick test								✓
Objective measures and samples: Paternal									
	Anthropometry^a,b,c^					✓Completed at any visit after birth			
	Skin prick test					✓Completed at any visit after birth			

*BV* bacterial vaginosis, *GBS* group B streptococcus, *OGTT* oral glucose tolerance test, *SCORAD* scoring atopic dermatitis

^a^height/length ^b^weight ^c^head circumference ^d^waist circumference ^e^excluding women with pre-existing diabetes

Questionnaires collect a range of data including confounders (such as previous GDM, parity etc.), effect modifiers (such as use of antibiotics, yoghurt etc.), outcome data, and adverse events.

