#### Assessment of secondary outcomes

##### Gestational diabetes mellitus

Women who are diagnosed with diabetes prior to 20 weeks gestation are excluded from the gestational diabetes outcomes for the study, as this diagnosis is likely to reflect pre-existing diabetes. Gestational diabetes outcomes are assessed at 26–28 weeks gestation, by a three time-point test 75 g oral glucose tolerance test (OGTT) recommended by international guidelines [25]. Preparation for the test include a 10–16 h pretest fast with instructions to avoid smoking during this time and during the test, and avoidance of exercise on the morning of the test. Participants remain in a resting state during the test which comprises of a baseline fasting blood sample, 75 g glucose load and blood samples at 1 and 2 h post load. An additional blood sample is collected at the time of the fasting blood test and this sample is separated and the serum stored at −80 °C for future analysis.

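### Weight gain is to enter the GDM model as an intermediate variable, but no maternal weight is scheduled between 14–16 weeks and birth, so it would be measured after the 26–28 week outcome

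*Protocol article*

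**What the plan says.** The Data analysis section of the protocol article compares GDM between arms by relative rates and a chi-squared test. It then adds an explanatory model, a generalised linear model with log link and binomial distribution: "The effect of weight gain will be investigated as an intermediate variable by adding it to the model". No start or end point for weight gain is given there.

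The timing of the other elements is fixed elsewhere in the article:

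- **Randomisation.** In the Abstract (Methods/design), women "will be enrolled in the study at 14–16 weeks gestation and randomised".
- **Outcome.** Under Assessment of secondary outcomes: "Gestational diabetes outcomes are assessed at 26–28 weeks gestation", by a 75 g oral glucose tolerance test (OGTT).
- **Maternal weight, Table 2.** The maternal anthropometry row, which includes weight by its footnotes, is ticked at 14–16 weeks, 3–7 days after birth, 6 months and 12 months. The 26–28 week, 35–37 week and birth columns are blank.
- **Maternal weight, Table 1.** The related outcomes for GDM include "Maternal anthropometric measures ^b^ at birth, and 6 and 12 months post-partum". The footnote restricts only height and head circumference to enrolment.

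**The concern.** An intermediate variable has to lie between the intervention and the outcome. Here that means weight change after randomisation at 14–16 weeks and no later than the OGTT at 26–28 weeks. The article schedules a weight at the start of that interval and none at its end. The next scheduled weight is taken at or shortly after birth.

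A gain computed from the scheduled weights therefore includes a stretch of pregnancy in which GDM status is already determined. Any influence of GDM on later weight then enters the model as though weight had influenced GDM. At stake is the reading of the explanatory analysis, namely whether HN001 lowers GDM through weight. The question will be read as substantive, because the Background reports lower maternal adiposity with probiotics in the same study population that motivates the GDM hypothesis.

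**Working it through.** **1. The plan's own figure.** The one stated number tied to this outcome is the 87% power under Sample size and power calculations. Inputs: control rate 15%; 63% reduction, so 0.15 × (1 − 0.63) = 0.0555; 200 per group less 2.5%, so 195; 5% level, taken as two-sided.

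- Difference: 0.15 − 0.0555 = 0.0945. Mean rate: 0.10275.
- Null standard error: √(2 × 0.10275 × 0.89725 / 195) = 0.03075.
- Alternative standard error: √((0.15 × 0.85 + 0.0555 × 0.9445) / 195) = 0.03037.
- Power: Φ((0.0945 − 1.96 × 0.03075) / 0.03037) = Φ(1.127) = 0.870.

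The 87% reproduces and is not in dispute.

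**2. Schedule against outcome.**

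| Time | Maternal weight scheduled | Event |
|---|---|---|
| 14–16 weeks | yes | randomisation, capsules start |
| 26–28 weeks | no | OGTT, GDM determined |
| 35–37 weeks | no | swabs |
| Birth or 3–7 days after | yes | delivery |
| 6 and 12 months | yes | follow-up |

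No pair of scheduled weights gives the gain from randomisation to the OGTT. Gain before 14–16 weeks precedes randomisation, so it cannot be an intermediate variable either.

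**3. Gap from OGTT to birth.** Gestation at birth is an assumption.

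- Birth at 38 weeks: 38 − 28 = 10 to 38 − 26 = 12 weeks.
- Birth at 40 weeks: 40 − 28 = 12 to 40 − 26 = 14 weeks.
- Birth at 37 weeks: 9 to 11 weeks, and less for preterm births.

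As a share of the enrolment-to-birth interval:

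- Birth at 38 weeks: 10/24 = 42% to 12/22 = 55%.
- Birth at 40 weeks: 12/26 = 46% to 14/24 = 58%.

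Roughly half the interval lies after the outcome. A weight taken after delivery also excludes the fetus and placenta.

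**4. Illustration of the consequence.** Assumptions, none from the article: weight gain has SD 5 kg and plays no mediating role; GDM lowers later gain by 0, 1, 2 or 3 kg. GDM rates are 15% and 5.55%. A simulation of 400,000 women used a log-link model fitted by Poisson quasi-likelihood. The crude treatment RR is 0.373.

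| GDM effect on later gain | Treatment RR after adding gain | RR of GDM per 5 kg gain |
|---|---|---|
| 0 kg | 0.373 | 1.01 |
| −1 kg | 0.374 | 0.84 |
| −2 kg | 0.378 | 0.70 |
| −3 kg | 0.385 | 0.61 |

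In the last row an arm difference in gain of 3 × 0.0945 = 0.28 kg also appears, although HN001 has no direct effect on weight. The association between weight and GDM is produced entirely by reverse causation. The treatment RR moves little: (ln 0.385 − ln 0.373) / |ln 0.373| is about 3% of the log effect.

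**The case against.** The strongest reply is that the Data analysis section never says which weights define the gain. The article is condensed: the anthropometry protocol sits in an additional file, a questionnaire is ticked at 26–28 weeks without its items being listed, and the variable for an exploratory model is often specified elsewhere. A pre-OGTT weight may therefore exist. This stands as a limit on certainty. It does not remove the conflict, because the article states both the analysis and the measurement schedule and mentions no other source of weight.

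Several stronger readings are tempting and are not supported:

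- **That a GDM diagnosis changes care and so changes weight.** The article does not say who receives the OGTT result or what follows it. This is only a possibility, and the timing problem does not depend on it.
- **That the adjustment would create or erase a treatment effect.** The illustration does not show this, since the treatment RR goes from 0.373 to 0.385 at most.
- **That the scheduled gain carries no relevant information.** By the same arithmetic, about 42–58% of the interval precedes the OGTT for births at 38–40 weeks. The measure is a contaminated proxy.
- **That the GDM result itself is compromised.** The relative rate and chi-squared comparison do not use weight gain.

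**Conclusion.** The concern holds in a limited form. The planned intermediate-variable analysis conflicts with the article's own schedule. As scheduled, weight gain ends about 10–14 weeks after the outcome for births at 38–40 weeks, is taken after delivery, and may partly reflect GDM. A statement either way about HN001 acting through weight gain would have no sound basis.

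The 10–14 weeks rest on the assumed gestation at birth. The conclusion also assumes that no pre-OGTT weight is collected outside what the article describes. The defect is confined to one explanatory model on a secondary outcome.

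**What to change.** Define the intermediate variable in the Data analysis section as a weight at or before the OGTT minus the 14–16 week weight, and name the source, for example clinic or maternity records. State how close to the OGTT the weight must be and how women without one are handled. If no such weight can be obtained, remove weight gain from the GDM model and report it by arm as an outcome only; the Abstract already lists it among the other outcome measures.

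Adding a weight to the 26–28 week visit is probably no longer possible. Trial status expects final outcome data by mid-2016, which, with a last infant visit at 12 months, puts the last births at about mid-2015 and the last OGTTs before that.

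The cost is a record lookup, with weights that are less standardised than study measurements and may be incomplete, or the loss of one exploratory model.
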